## Abstract

People with multiple myeloma (MM) are second only to people with lung cancer for the poorest reported health-related quality of life (HRQoL) of all cancer types. Whether exercise can improve HRQoL in MM, where bone pain and lesions are common, requires investigation. This trial aims to evaluate the efficacy of an exercise intervention compared with control on HRQoL in people with MM. Following baseline testing, people with MM (*n* = 60) will be randomized to an exercise (EX) or waitlist control (WT) group. EX will complete 12-weeks of supervised (24 sessions) and unsupervised (12 sessions) individualized, modular multimodal exercise training. From weeks 12–52, EX continue unsupervised training thrice weekly, with one optional supervised group-based session weekly from weeks 12–24. The WT will be asked to maintain their current activity levels for the first 12-weeks, before completing the same protocol as EX for the following 52 weeks. Primary (patient-reported HRQoL) and secondary (bone health and pain, fatigue, cardiorespiratory fitness, muscle strength, body composition, disease response, and blood biomarkers) outcomes will be assessed at baseline, 12-, 24- and 52-weeks. Adverse events, attendance, and adherence will be recorded and cost-effectiveness analysis performed. The findings will inform whether exercise should be included as part of standard myeloma care to improve the health of this unique population.

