We aim to investigate the influence of an individualized supervised exercise intervention on HRQoL in people with MM compared with usual care. The effects of exercise on outcomes that may influence HRQoL (i.e., fatigue, bone pain, cardiorespiratory fitness, bone health, muscle strength, body composition, and balance), as well as the influence of exercise on markers of bone turnover, adipokines, immune functioning, and metabolomics will be compared with usual care. Adverse events, attendance, and adherence will be recorded and a cost-effectiveness analysis performed. Finally, after twelve weeks of supervised exercise and a further twelve weeks of a stepped-down supervision approach, the maintenance of the effect of exercise six months after cessation of all exercise support will be explored. It is hypothesized that a 12-week supervised exercise intervention will improve HRQoL, and factors that influence HRQoL, in people with MM compared with usual care. Exercise is also hypothesized to improve markers of bone turnover, adipokines, immune functioning, and metabolomic profiles compared with usual care. These effects are hypothesized to return to baseline levels six months after cessation of all exercise support.

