### 2.1. Trial Design and Setting

The study design is depicted in Figure 1. People diagnosed with MM will be invited to participate in this multi-site, single blind, randomized waitlist-controlled trial. A waitlist control group design was chosen to reduce participant dropout from a non-exercise control group [39]. Participants randomized to the waitlist control group will be encouraged to maintain their customary physical activity during the 3-month wait period.

The exercise program follows a stepped down supervisory approach with reduced supervision after three months. All participants will complete an assessment battery (see Table 1) at baseline, at the end of the supervised phase, and at 6- and 12-months following baseline testing (see Figure 1).

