## 5. Statistical Considerations and Data Analyses

A priori power calculations determined that a sample of 44 participants (*n* = 22 per group) will be needed to detect a mean difference of 6.7 points [51] between groups on the EORTC QLQ-C30 MY20 after the 3-month supervised exercise phase, with 80% power and 5% alpha. To account for an anticipated dropout rate of 25%, 60 participants will be recruited to the study. A difference of 6.7 on the physical function subscale of the EORTC QLQ-C30 MY20 questionnaire, determined by receiver operating characteristic curve analysis, corresponds to the minimum clinically meaningful change considered important by people with MM [51].

Data will be analyzed using the Stata statistical software package (version 15.0, StataCorp, College Station, TX, USA). Data entry will be performed in duplicate, and accuracy will be assessed with automatic cross-checking procedures. Range checks for data values will be performed to promote data quality. Data will be assessed for normality using the Shapiro–Wilk test. Subsequent analyses will include standard descriptive statistics, *t* tests, correlation, regression, and one-way repeated measures ANOVA or the comparable non-parametric test as necessary to examine differences among timepoints. Each model will include covariates, as appropriate, and will be adjusted using the baseline value as a fixed continuous covariate. For accelerometer data, means and 95% confidence intervals will be calculated and repeated measures accounted for across multiple days within participants. Quality of life questionnaire items will be analyzed using random effects mixed modelling with Fisher’s least significant difference tests for post hoc analyses to compare mean changes in outcomes between groups at each assessment period, with time and group as the fixed factors. A time × group interaction term will be used to formally test for differences between groups (alpha = 0.05).

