### Cost-Effectiveness Analysis

Cost-utility analysis (CUA) will be used to explore whether the intervention provides health benefits at the individual level. CUA compares the incremental costs and benefits, expressed in quality-adjusted life years (QALYs) gained, of alternative programs. Health utilities will be derived from the EORTC QLU-C10D, a subset of 10 questions from the EORTC QLQ-C30 [110]. Costs will be obtained from a questionnaire that will be completed by the waitlist control and exercise groups prior to commencement of the intervention and during the 3-month supervised and 6-month unsupervised phases to determine individual costs associated with the intervention and other health resource utilization. Costs will be measured from a societal perspective and will include intervention costs, healthcare costs, costs of informal care, sports costs, unpaid productivity costs, and absenteeism costs. Healthcare costs include the costs of primary healthcare (i.e., general practice, physical therapist), secondary healthcare (i.e., outpatient care, hospitalization), and prescribed, as well as over-the-counter medication. The value of the resources consumed will be determined using unit prices from standard costing resources (e.g., Medicare Benefits Schedule, award wage schedules).

Resource utilization during the 3-month supervised and 6-month unsupervised phases will be recorded. This includes labor (e.g., to deliver the intervention and group classes) and non-labor (e.g., gymnasium use), as well as the cost of usual care provided by the hospital. Resource use will be costed at market rates (e.g., industrial award rates for labor costs) for use in cost-effectiveness analyses. The resource use associated with the exercise intervention delivery will include labor time, i.e., AEP hours planning the exercise sessions (e.g., phoning/meeting people to book their session, pre-exercise safety screening), delivering the exercise sessions, and documentation time for clinical notetaking. Time spent for research assessments will not be included. Resource use will also include non-labor costs associated with delivering the intervention from the perspective of the health service, e.g., cost of hiring gym space.

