^a^ Baseline testing battery is repeated for waitlist control group after three months of usual care. ^b^ PACES-8 survey will be administered at 4-, 8-, and 12-weeks during the exercise intervention. ^c^ Adherence and safety will be monitored continuously throughout the supervised and unsupervised intervention. EORTC QLQ-C30: European Organisation for Research and Treatment of Cancer Quality of Life Questionnaire Core 30; EORTC QLQ-MY20: European Organisation for Research and Treatment of Cancer Quality of Life Questionnaire—Multiple Myeloma module; DXA: Dual energy X-ray absorptiometry; pQCT: Peripheral quantitative computed tomography; BMI: Body mass index; 30 STS: 30-s sit-to-stand test; YBT: Y-Balance Test; BPI: Brief Pain Inventory; FACT-BP: Functional Assessment of Cancer Therapy—Bone Pain; FACIT-F: Functional Assessment of Chronic Illness Therapy—Fatigue; OLBPDQ: Oswestry Low Back Pain Disability Questionnaire; PRO: Patient-reported outcomes; FACT-MM: Functional Assessment of Cancer Therapy—Multiple Myeloma; MyPOS: Myeloma Patient Outcome Scale; FES-I: Falls Efficacy Scale—International; PACES-8: Physical Activity Enjoyment Scale 8.

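### Between-group quality-of-life tests are not confined to week 12, although the waitlist arm then starts the same programme; later contrasts compare immediate with delayed exercise, not exercise with usual care

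*Protocol article*

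**What the plan says.** Section 5 analyses the quality-of-life questionnaires, which include the primary instrument, by a random effects mixed model with post hoc tests "to compare mean changes in outcomes between groups at each assessment period, with time and group as the fixed factors". The formal test follows: "A time × group interaction term will be used to formally test for differences between groups (alpha = 0.05". Each model is also adjusted for the baseline value. Nothing restricts either comparison to the 12-week visit.

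The Abstract has WT keep its usual activity for 12 weeks "before completing the same protocol as EX for the following 52 weeks". Section 2.1 confirms a 3-month wait.

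Visit timing is described in three ways:
- Abstract: outcomes "will be assessed at baseline, 12-, 24- and 52-weeks".
- Section 2.1, for all participants: "at baseline, at the end of the supervised phase, and at 6- and 12-months following baseline testing".
- Table 1, footnote a: "Baseline testing battery is repeated for waitlist control group after three months of usual care".

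Section 3.1 defines the primary outcome as quality of life after the 3-month supervised phase compared with the waitlist control. The Introduction adds a maintenance hypothesis: "These effects are hypothesized to return to baseline levels six months after cessation of all exercise support".

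The Cost-Effectiveness Analysis section describes incremental costs and QALYs of alternative programmes, with both groups completing a cost questionnaire "prior to commencement of the intervention and during the 3-month supervised and 6-month unsupervised phases".

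**The concern.** Randomisation gives a comparison with usual care only while one arm receives usual care, which is the first 12 weeks. The analysis text treats all post-baseline visits alike. An EX–WT difference at week 24 or 52, or an interaction across visits, could then be reported as an effect of exercise, or as its disappearance, when it reflects when each arm started.

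Two further gaps add to this. WT has two baseline batteries, and the text does not say from which one its 6- and 12-month visits run, or which one is the covariate. The cost section also does not name the wait, the only usual-care period, among its costing phases. At stake are the conclusions at 24 and 52 weeks and the economic comparison, not the primary result.

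**Working it through.** **1. Sample size.** Section 5 needs 44 evaluable participants (22 per group) and allows 25% dropout. 22 / 0.75 = 29.3, so 30 per group and 60 in total, as stated. This is sized for the 3-month contrast only, so confining the test to week 12 leaves it unchanged.

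**2. Programme exposure by visit** (Abstract: WT starts at week 12 and continues for 52 weeks, so it ends at 12 + 52 = week 64).

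| Weeks from randomisation | EX exposure | WT exposure | What the contrast estimates |
|---|---|---|---|
| 12 | 12 | 0 | exercise versus usual care |
| 24 | 24 | 12 | immediate versus delayed start |
| 52 | 52 | 40 | immediate versus delayed start |

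If WT's visits instead run from its repeat baseline, its 24- and 52-week visits fall at weeks 12 + 24 = 36 and 12 + 52 = 64 from randomisation, and both arms have equal exposure at each. On the first clock, WT's end of supervised phase (week 24) coincides with its 6-month visit. The text does not choose between the clocks.

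**3. What a late difference identifies.** Let a be EX's gain and b be WT's gain over what no exercise would have given. The contrast estimates a − b. At week 12, b = 0. Later, take the protocol's 6.7 points:
- EX keeps its benefit and WT catches up: 6.7 − 6.7 = 0.
- EX loses its benefit and WT gains nothing: 0 − 0 = 0.

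Opposite histories give the same expected result.

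**4. Size, by illustration.** No SD is given. Solving 22 per group, 6.7 points, 80% power and two-sided 5% for the SD gives 7.93 (normal approximation) or 7.75 (noncentral t). With 7.75, the standard error of a visit difference is 7.75 × √(2/22) = 2.34. Correlation between visits is assumed to be 0.3–0.7.

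Suppose the true differences are 6.7, 0 and 0 (full WT catch-up by week 24):
- Power by visit (normal approximation): 82%, 5%, 5%.
- With baseline as a covariate, the interaction asks whether the group difference changes across the three post-baseline visits. Its noncentrality is Σ(d − mean d)² / [SE² × (1 − ρ)]. The mean is 6.7 / 3 = 2.23 and the sum of squares is 6.7² × 2/3 = 29.9. Dividing by 5.46 × (1 − ρ) gives about 7.8, 11.0 and 18.3 for ρ = 0.3, 0.5 and 0.7. Power on 2 df is 71%, 85% and 98%.

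With half catch-up at week 24 and full catch-up at week 52 (6.7, 3.35, 0), interaction power is 57–92%.

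If the control arm had stayed untreated and EX had kept 6.7 throughout, the same test would reject only 5% of the time, because the difference never changes. So on this coding the interaction responds to a change in the gap between arms and not to the benefit of exercise. This result depends on baseline being a covariate and not a level of the time factor.

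**5. Costing phases.** The Abstract runs unsupervised training from week 12 to week 52, which is 40 weeks. The stepped-down supervision section splits this into three months with optional classes and six months without, about nine months. The cost section names a 6-month unsupervised phase and also costs group classes. If that phase includes the classes, the last three months are uncosted. If it starts at month 6, the classes fall outside the named phases.

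**The case against.** The strongest reply is that the primary contrast is already fixed, and this stands. Section 3.1 defines it against the waitlist control after three months, Section 5 sizes the trial on it, the Discussion treats WT activity in the first 12 weeks as the threat to it, and Table 1 footnote a schedules WT's battery after three months of usual care. A reader might infer from Section 2.1 that WT's 3-month value is taken after its own supervised phase, so that the primary test compares two exercised arms and rejects only 5% of the time. The documents do not support this: those four places contradict it, and Table 1 does not tie its 3-month column to the end of the supervised phase.

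It is also fair that the interaction test keeps power under catch-up (step 4). The fault is what a significant result would mean, not loss of power.

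A reader might infer that a closing EX–WT gap would be taken as confirming the maintenance hypothesis. That hypothesis concerns a return to baseline levels, and Section 5 also plans comparisons among timepoints, so the between-group contrast is not its only test.

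After week 12 the arms remain a valid randomised comparison of immediate with delayed start. Figure 1, not shown here, may settle WT's visit clock.

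On costs, neither comparator arm nor horizon is fixed, so a definite bias towards zero, or a stated share of the horizon lacking a control, cannot be derived. The 6-month phase may mean the final unsupported months. The omission of the wait as a named costing phase and the unclear mapping remain.

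**Conclusion.** The point holds in a limited form and should be fixed. Between-group quality-of-life testing is not restricted to the one visit at which WT is a usual-care control. The 12-week primary contrast and the sample size of 60 are unaffected. At 24 and 52 weeks from randomisation the contrast is immediate versus delayed exercise. A null result there cannot separate loss in EX from gain in WT, and a significant interaction may show only that WT caught up.

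The exposure table and the identification argument rest on the protocol's own schedule. The 71–98% figure rests on an SD back-solved from the sample size, 22 evaluable per group, correlations of 0.3–0.7, full catch-up by week 24 and baseline as a covariate; it is an illustration. WT's clock is unsettled in the visible text only. The cost-utility part is weaker because it is partly inferred.

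**What to change.** - **Clock and baseline.** Time the randomised comparison from randomisation in both arms, and use the pre-randomisation value as the baseline covariate.
- **Formal test.** Make it the group difference at week 12 from the mixed model: EX at week 12 against WT's repeat battery, taken before WT starts exercise.
- **Later visits.** Report 24- and 52-week results as within-participant change from the start of exercise, with 95% confidence intervals, labelled non-randomised. Label any later EX–WT contrast as immediate versus delayed start.
- **Cost-utility analysis.** Name WT's 3-month wait as a costing period, base the incremental comparison with usual care on those 12 weeks, and label longer horizons as descriptive or modelled. Reconcile the 6-month unsupervised phase with the Abstract and the stepped-down supervision section.

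The cost is analysis wording plus one cost questionnaire for WT at a visit that already exists; recruitment does not change. The trial gives up a controlled claim after week 12, which the design cannot support. Within-participant change also carries any underlying trend in disease or treatment, hence the non-randomised label.

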## 1. Introduction

Recent remarkable advances in treatments for people with multiple myeloma (MM), an incurable cancer of plasma cells, are contributing to longer life expectancies [1]. However, the inevitable relapse and substantial disease- and treatment-related side effects can reduce patients’ health-related quality of life (HRQoL). In a recent population-wide study, people with MM had the most functional limitations and were second only to lung cancer for the highest psychological distress and lowest quality of life of all cancer types [2]. HRQoL has been shown to correlate with all-cause mortality in all disease stages of MM [3,4,5,6,7].

Exercise has been shown to be an effective therapy for improving HRQoL in other cancer patient populations both during and following treatment [8]. However, whilst these short-term benefits of exercise have been consistently reported, the maintenance of these benefits beyond the completion of interventions is understudied. In people with MM, only one intervention published as a single arm study [9] and later a randomized controlled trial [10] has explored the effects of aerobic and/or resistance exercise on HRQoL. The randomized controlled trial failed to find any effect of exercise on HRQoL. The lack of effect may be explained, at least in part, by low attendance to the prescribed intervention, i.e., once-weekly group classes at a hospital outpatient gym (only 80% attending >50% of sessions) and twice weekly home-based exercise (completion rates not reported). Adherence to the prescribed protocol was not reported for either the supervised or unsupervised sessions. Thus, the exercise dose received was lower than that prescribed and potentially insufficient to elicit benefits to HRQoL. Individualized supervised exercise sessions have been found to result in greater adherence and better outcomes compared with unsupervised/home-based sessions for people with cancer [11]. Therefore, future research is required which investigates the effect of an individualized supervised exercise intervention on the HRQoL of people with MM.

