### 3.1. Primary Outcome

#### Cancer-Specific Quality of Life (EORTC QLQ-C30 and QLQ-MY20)

The primary outcome of this study is HRQoL after the 3-month supervised exercise intervention compared with the waitlist control. HRQoL will be measured using the overall HRQoL summary score for the core HRQoL questionnaire of the European Organisation for Research and Treatment of Cancer Quality of Life Questionnaire (EORTC QLQ-C30, version 3.0) [46]. The EORTC QLQ-C30 is a widely used and well-validated cancer-specific instrument [3] with good psychometric properties in solid tumors [47,48]. It has acceptable reliability and validity in MM (Cronbach’s α = 0.70–0.92, except role function = 0.54), with an excellent ability to discriminate between patients in different objective disease states and a high responsiveness to changes in patients’ clinical status over time [3,49]. In a recent Delphi analysis, consensus was reached to collect patient-reported outcomes using the EORTC QLQ-C30 in patients with MM [50]. The minimal important difference (MID), defined as the smallest change in a HRQoL score considered important to patients that would lead the patient or clinician to consider a change in therapy, will be based on those estimated for individual scales of the QLQ-C30 in patients with MM [51].

The EORTC QLQ-C30 summary score encompasses all symptom (e.g., fatigue, pain) and function domains (e.g., emotional and social functioning) assessed by the QLQ-C30. The summary score is a strong prognostic factor for overall survival above and beyond that provided by clinical and sociodemographic variables for patients with MM [7]. The summary score also appears to have more prognostic value than the global QoL, physical functioning, or any other scale within the QLQ-C30 [7].

The European Organisation for Research and Treatment of Cancer Quality of Life Questionnaire Multiple Myeloma module (EORTC QLQ-MY20) is a reliable and valid instrument, recommended as a supplement to the QLQ-C30 instrument in patients with MM (Cronbach’s α = 0.70–0.92) [52]. As with the QLQ-C30, QLQ-MY20 domain scores are averaged and transformed linearly to a score ranging from 0–100. A high score for disease symptoms and side effects of treatment represents a high level of symptomatology or problems, whereas a high score for future perspective and body image represents better outcomes.

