#### 3.3.2. Feasibility and Adherence

The feasibility of the program will be measured by the rates of eligibility, recruitment, attrition, attendance (defined as: n _sessions attended_ × n _sessions prescribed_^−1^ × 100), and adherence to the program intensity and duration for each component of the intervention, i.e., aerobic, resistance and bone loading.

Attendance at the supervised sessions will be recorded by the supervising AEP, in addition to the self-reported completion of the weekly home-based session. Adherence records will be completed by the supervising AEP at each supervised session with detailed reasons for non-adherence recorded. Adherence to the aerobic component of the protocol will be defined as: minutes at the workload prescribed by the AEP, i.e., 12 min at moderate-to-vigorous intensity (60–85% HR_peak_) and 8 min at high intensity (>85% HR_peak_). Adherence to the resistance training component of the protocol will be defined as: minimum of 80 repetitions (5 exercises, 2 sets, 8 repetitions = 5 × 2 × 8) at a minimum intensity of 5/10 on the OMNI-RES scale [44]. Adherence to the bone loading component of the protocol will be defined as: minimum of 80 repetitions. The minimum intensity for adherence will be 2, where 1: isometric exercise targeting spine and/pelvis; 2: marching; 3: stomping; 4: jumping; 5: drop jump from height (range 10–30 cm). Unilateral exercises, i.e., marching, stomping, will have a minimum of 80 impacts per leg (4 × 20 impacts per leg), with a minimum of 80 total impacts for bilateral exercises, i.e., jumping, drop jumping from height.

*A**priori* cut points were defined to determine successful adherence to each component of the exercise program. Cut-off values for the feasibility criterion (a recruitment rate of ≥25% [106]; an attrition rate of <25% [107]; and attendance and adherence of ≥75% [108]) were established *a priori* as clinically relevant based on previous studies in other cancers.

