The number of participants who provide data at each timepoint will be reported, with reasons as to why participants did not attend. Incomplete data and missing values will primarily be managed using intention-to-treat analyses, using a 70% cut-point for adherence. To ensure the robustness of the findings, a secondary sensitivity analysis will be performed [109]. Non-continuous data will be analyzed using multinomial logistic regression. Metabolomics and lipidomics data will be evaluated using multivariate statistics, including principal component analysis and sparse partial least squares discriminant analysis. The blood molecular time-series measures will be analyzed to determine the metabolic and immune pathways altered by exercise and to determine biomarkers of responders for physical fitness, fatigue, and pain, if any. Exercise and control groups will be further stratified by therapy and remission duration. All tests will be two-tailed, and an alpha level of 0.05 will be applied as the criterion for statistical significance. There are no interim analyses planned or early trial termination guidelines.

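### The primary analysis is labelled intention-to-treat but carries an undefined 70% adherence cut-point; if it excludes participants, it can exclude only exercise participants

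*Protocol article*

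**What the plan says.** The rule is in Section 5 (Statistical Considerations and Data Analyses): "Incomplete data and missing values will primarily be managed using intention-to-treat analyses, using a 70% cut-point for adherence". The next sentence promises a secondary sensitivity analysis with a literature reference, but names no population or method and does not mention the cut-point. Earlier in Section 5, quality-of-life data are assigned to a random-effects mixed model with time, group and their interaction.

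Three other places determine how the rule would act:

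- **Primary comparison (Section 3.1):** "The primary outcome of this study is HRQoL after the 3-month supervised exercise intervention compared with the waitlist control".
- **Control arm until then (Abstract):** "The WT will be asked to maintain their current activity levels for the first 12-weeks". Section 2.1 says the same of the wait period.
- **Adherence (Section 3.3.2):** it is defined only for the aerobic, resistance and bone-loading components of the programme. "Adherence records will be completed by the supervising AEP at each supervised session with detailed reasons for non-adherence recorded".

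Section 3.3.2 also lists, among its feasibility benchmarks, "attendance and adherence of ≥75" per cent.

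**The concern.** Intention-to-treat means that participants are analysed as randomised, whatever they did afterwards. A cut-point on adherence is a condition on post-randomisation behaviour and cannot be part of it. The word primarily in the sentence places the cut-point in the main analysis, and nothing assigns it to the sensitivity analysis.

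An analyst following the sentence could drop exercise participants below 70%, keep every waitlist participant, and report the result as intention-to-treat. The protocol gives reasons to expect that those dropped would be less well. Section 2.5 cancels or postpones sessions for fever, infection, low blood counts and cardiac complications. It also assigns isometric work, level 1 of the loading scale, to participants with certain bone lesions, while Section 3.3.2 counts bone-loading adherence only from level 2. Low recorded adherence can therefore reflect illness or lesions rather than reluctance. At stake is the validity of the primary quality-of-life result, which is meant to inform whether exercise enters standard myeloma care.

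**Working it through.** **1. Can the waitlist arm fail the cut-point?** The primary comparison is at 3 months. Until then the waitlist arm is asked only to keep to its current activity. Adherence is scored against programme components that this arm has not yet been prescribed. It has no adherence value at the primary time point, so any filter acts on the exercise arm alone.

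**2. The plan's own sample size.** Section 5 gives 22 per group, a 6.7-point difference, 80% power, 5% alpha (two-tailed), 25% dropout and 60 recruited.

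- 44 / (1 − 0.25) = 58.7, so 59. Per arm, 22 / 0.75 = 29.3, so 30, and 2 × 30 = 60. The stated 60 is reproduced.
- No SD is stated. With 22 per group, 80% power in a two-sample t test needs a standardised difference of 0.865, which implies an SD of 6.7 / 0.865 = 7.75. This back-solved SD is used below.

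**3. Bias if the cut-point excludes.** Let q be the share of the exercise arm removed and d the points by which those removed would score worse than those kept, regardless of treatment. If those kept have mean m, the full-arm mean is (1 − q)m + q(m − d) = m − qd. Removal raises the exercise mean, and so the group difference, by q × d.

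The documents give neither q nor d. The ranges below are assumptions: q from 10% to 40%, d from 0 to 10 points.

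| q | d = 0 | d = 3 | d = 5 | d = 10 |
|---|---|---|---|---|
| 10% | 0 | 0.3 | 0.5 | 1.0 |
| 20% | 0 | 0.6 | 1.0 | 2.0 |
| 30% | 0 | 0.9 | 1.5 | 3.0 |
| 40% | 0 | 1.2 | 2.0 | 4.0 |

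The largest value, 4.0, is 4.0 / 6.7 = 60% of the target difference. With no true effect, SD 7.75 and 22 waitlist participants, the two-sided type I error stays at 5% when d = 0. It is about 6.8% at q = 20%, d = 5, and reaches 29.9% at q = 40%, d = 10.

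**4. Power if the exclusions come on top of dropout.** Waitlist n = 22, true difference 6.7, SD 7.75, no bias:

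| q | Exercise n | Power |
|---|---|---|
| 0 | 22 | 80% |
| 10% | 20 | 78% |
| 20% | 18 | 75.5% |
| 30% | 15 | 71% |
| 40% | 13 | 67% |

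Starting from 22 assumes that the poor adherers are different people from the 25% already allowed for as dropouts. If they overlap, the loss is smaller. If every poor adherer is also a dropout, there is no loss beyond the plan's own allowance.

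**The case against.** The strongest reply is that the sentence never says participants below 70% are excluded. The cut-point might have been meant for the sensitivity analysis or for a rule on imputing missing scores. A reader might infer that the primary analysis is definitely a per-protocol one; the text does not establish that. This part of the reply stands, and the consequences above are conditional on the exclusion reading. It does not rescue the sentence, because no other meaning is stated and the label and the cut-point still conflict.

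Three further stronger readings fail:

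- **That 70% contradicts 75%.** The 75% in Section 3.3.2 is a feasibility criterion, listed beside recruitment and attrition benchmarks. It is not a rule on who is analysed, and different thresholds for different purposes need not conflict. Their relation merely needs explaining.
- **That the Introduction supplies the excluded share.** The earlier myeloma trial had "only 80% attending >50% of sessions", but that describes attendance at once-weekly group classes. The Introduction says adherence was not reported there, and the present trial uses more supervision in response.
- **That a bias of several points is to be expected.** The score deficit has no source in the documents, and with no deficit there is no bias.

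It is also fair to say that a mixed model is already planned, so the protocol does not rely on the intention-to-treat label alone to deal with missing scores. Further missing-data sensitivity methods can be left to the analysis plan.

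**Conclusion.** The point holds as a contradiction in the current text: an adherence cut-point of unstated function is attached to a primary analysis called intention-to-treat. This is not a detail left for later, since the article fixes the rule and fixes it against its own label. That only the exercise arm could be affected follows from the waitlist design and the adherence definitions, and needs no assumption.

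The size is conditional. If the cut-point excludes 10–40% of the exercise arm and those removed would score 0–10 points worse, the bias towards exercise is 0 to 4.0 points against the 6.7-point target. If the exclusions come on top of planned dropout, power falls from 80% to about 78–67%. These figures rest on assumed shares and deficits and on a back-solved SD of 7.75. They show what the wording permits, not what will happen.

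**What to change.** Rewrite the sentence in Section 5 to say that the primary analysis includes all randomised participants in their assigned arm, regardless of attendance or adherence, using all available scores in the mixed model already specified in that section. Delete the 70% cut-point from it.

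If an adherence-based analysis is wanted, name it as secondary or sensitivity, say what the threshold does and to which measure it applies, and explain how it relates to the 75% feasibility criterion in Section 3.3.2.

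The cost is one sentence and minor programming, with no extra participants or data. The estimated effect may be slightly smaller, because poor adherers stay in the exercise arm.
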